#### Statistical analysis plan

2.9.2

All statistical analyses will be conducted in accordance with the intention-to-treat principle. That is, all randomized patients will be analyzed in the groups to which they were originally allocated. Researchers performing statistical analysis will be blinded to the cluster grouping.

Categorical variables will be presented as numbers and percentages and compared using the chi-squared test or Fisher’s exact test. For continuous variables, normal distribution will be checked by Kolmogorov–Smirnov Test, and presented as mean and standard deviation or median and interquartile range, as appropriate. Comparison of continuous variables will be performed by Student’s *t*-test for normally distributed variables and the Mann–Whitney U test for non-normally distributed variables.

Time-to-event variables will be analyzed using survival analysis, and the difference between groups will be assessed with the log-rank test.

The patients will be stratified *a priori* into subgroups with:

high versus intermediate and low respiratory drive according to the P0.1 criteria reported by a previous study (29);diagnosis of acute respiratory distress syndrome (ARDS) versus non-ARDS according to the Global definition (35);long versus short duration of controlled ventilation before enrollment according to the median obtained in all enrolled patients.

Statistical analyses will be performed using MedCalc (2022 MedCalc Software Ltd., Belgium). A *p* value of less than 0.05 is considered statistically significant.

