### Randomization

2.2

The randomization will be performed by a statistician who will not be involved in the study procedures. To improve power and balance, the 16 participating ICUs (clusters) are matched in pairs with a similar number of beds and volume of patients undergoing mechanical ventilation (22). The ICUs are randomized within the pairs with a 1:1 ratio to either the PMI-targeted (*n* = 8) or VT/RR-targeted (*n* = 8) group.

Due to the nature of the intervention and control, it is not possible to blind participating ICUs, personnel providing patient care in the ICU, and researchers performing data collection. However, the researchers who conduct the statistical analyses will be blinded to the grouping.

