#### Sample size estimation

2.9.1

Our previous studies showed that the mean (± standard deviation) VFDs in Chinese academic hospitals was 19 ± 3.3 days (19, 20). An individual RCT will require 342 patients to detect a one-day increase in VFDs with a type I error (Alpha) of 0.05 and a power of 80%. According to previous studies, an intra-cluster correlation coefficient of 0.03 is used to calculate the sample size for the cluster RCT (33, 34), which results in a target of 551 recruited patients. Accounting for 15% of immeasurable PMI during PSV (19, 20), a sample of 648 will be the target, with an approximate average recruiting 40 patients in 16 participating ICUs.

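### ICUs are randomised and the sample size assumes an ICC of 0.03, but the stated tests treat patients as independent: at that ICC, with no gain from matching, the 5% test of VFDs has a true type I error of about 17–18%

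*Protocol article*

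**What the plan says.** Three parts of the protocol article bear on this.

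- **Randomization (2.2).** The ICU is the unit of allocation: "the 16 participating ICUs (clusters) are matched in pairs with a similar number of beds and volume of patients undergoing mechanical ventilation". Then: "The ICUs are randomized within the pairs with a 1:1 ratio". This gives eight ICUs per group.
- **Sample size estimation (2.9.1).** "An individual RCT will require 342 patients to detect a one-day increase in VFDs", based on a VFD mean and SD of 19 and 3.3 days. For the cluster design, "an intra-cluster correlation coefficient of 0.03 is used to calculate the sample size for the cluster RCT". The total goes from 342 to 551, and to 648 after a 15% allowance for immeasurable PMI, or about 40 patients per ICU.
- **Statistical analysis plan (2.9.2).** For continuous variables: "Comparison of continuous variables will be performed by Student’s *t*-test for normally distributed variables and the Mann–Whitney U test for non-normally distributed variables". A Kolmogorov–Smirnov test decides which of the two is used. Categorical variables are compared by chi-squared or Fisher's exact test. For time-to-event variables, "the difference between groups will be assessed with the log-rank test". The significance threshold is 0.05.

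No separate test is given for the primary outcome, so VFDs fall under the t-test/Mann–Whitney sentence. No section mentions a mixed model, GEE, cluster-robust variance, an ICU-level summary or a pair term. The only mention of clusters in 2.9.2 concerns blinding of the analysts.

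**The concern.** The design and the sample size both accept that patients in the same ICU resemble each other. The tests in 2.9.2 are valid only if they do not. When whole ICUs are allocated, differences between ICUs enter the difference between groups, but a patient-level test does not count them in its standard error. The standard error is then too small, the p-value too low and the confidence interval too narrow.

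The introduction says that a positive result could change ventilation practice. Under the stated analysis, a p-value below 0.05 for VFDs would not carry the false-positive risk that the protocol claims for it.

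A lesser issue sits in the same paragraph. The trial is powered on a one-day difference in means, but a normality pre-test decides whether a mean difference is what gets tested.

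**Working it through.** **Inputs from the protocol.** 16 ICUs in 8 pairs; SD 3.3 days; target difference 1 day; alpha 0.05 (taken as two-sided, which reproduces the stated total); power 80%; ICC 0.03; totals 342, 551 and 648.

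**1. Reproducing the stated sample size.**
- Individual trial: n per group = 2 × (1.960 + 0.842)² × 3.3² / 1² = 170.9, so 171 per group and 342 in total.
- Cluster step: 342 × [1 + (342/16 − 1) × 0.03] = 342 × 1.611 = 551.
- Allowance: 551 / 0.85 = 648.2.

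The chain 342 → 551 → 648 reproduces, so the ICC of 0.03 is indeed built into the plan.

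**2. True type I error of a patient-level test.** With m patients per ICU and equal cluster sizes, the variance of the group difference is DE = 1 + (m − 1) × ICC times what the test assumes. The true error of a nominal 5% test is 2 × [1 − Φ(1.96/√DE)], and the interval is too narrow by √DE.

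| Patients per ICU | DE at ICC 0.03 | √DE | True type I error |
|---|---|---|---|
| 551/16 = 34.4 | 2.00 | 1.42 | 16.6% |
| 40 | 2.17 | 1.47 | 18.3% |
| 648/16 = 40.5 | 2.185 | 1.48 | 18.5% |

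**3. Check by simulation.** With 16 ICUs of 40, normal data, ICC 0.03, no treatment effect and no pair effect, separate sets of 2,000 to 6,000 runs gave these rejection rates:
- patient-level t-test: 17.4–19.1%;
- Mann–Whitney: 16.7–19.2%;
- unpaired t-test on ICU means (14 df): 5.2–5.5%;
- paired t-test on the eight pairs (7 df): 5.2–5.3%.

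**4. Sensitivity to the matching.** Suppose pairing absorbs a share s of the between-ICU variance. The protocol gives no value for s, so the shares below are assumptions. Then DE = (1 − ICC) + m × ICC × (1 − s).

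| Assumed share s | DE, m = 34.4 to 40.5 | True error by formula | Simulated, m = 34 to 40 |
|---|---|---|---|
| 25% | 1.75 to 1.88 | 13.8–15.3% | 13.4–14.9% |
| 50% | 1.49 to 1.58 | 10.8–11.9% | 11.0–12.0% |
| 75% | 1.23 to 1.27 | 7.7–8.2% | 7.4–8.6% |

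**5. Sensitivity to the ICC.** With no gain from matching and m = 34.4 to 40.5, an assumed ICC of 0.01 gives 9.0–9.7%, 0.02 gives 12.9–14.3%, and 0.05 gives 23.1–25.6%.

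**6. Power of a valid analysis at 648 patients.** The standard error is 3.3 × √(4 × 2.185/648) = 0.383 days. Power for one day is Φ(1/0.383 − 1.96) = 74% by the normal approximation. It is 68% with t on 14 df and 61% with t on 7 df when matching brings no gain.

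**The case against.** **A fuller analysis plan may exist, and an article condenses it.** That would excuse silence. Here the article names the tests, and they do not fit the design. One might read the t-test as a test on ICU means, but the section says that all randomised patients will be analysed, and Fisher's test on counts and the log-rank test work on patients.

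**The size of the error is conditional.** This stands. A reader might infer that the type I error is 17–18% without qualification. That figure needs an ICC of 0.03 for VFDs and no gain from matching on beds and ventilated-patient volume. It is smaller if matching works, but in every case examined it stays above 5%.

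**The figure does not carry over to secondary outcomes.** This stands. The ICC is used only to size the VFD comparison, and none is given for mortality, reintubation or length of stay. Only the direction of the error is known.

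**Ignoring the pairs is not in itself an error of validity.** This stands. In the simulations an unpaired t-test on ICU means rejected 5.2–5.5% of the time with no pair effect and about 2–4% with one, so it is conservative. With eight pairs, breaking the match can be defended. The choice affects power and should be prespecified.

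**VFDs need not have a large spike at zero.** A reader might infer that many zero values guarantee failure of the normality test, so that the mean difference is never tested. The protocol's figures do not support this. At a mean of 19, a share p of zeros forces an SD of at least 19 × √[p/(1 − p)]; 20% zeros would need 9.5 days, and 3.3 days allows at most about 3%. What stands is narrower: the choice of primary test is left to a pre-test.

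**The document does not say that the named software, MedCalc, cannot fit suitable models.** This stands. That needs confirming, not assuming.

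**Conclusion.** The plan is wrong as written and must be changed before analysis. The article randomises ICUs and sizes the trial for correlation within them, then states tests that ignore the ICU for every outcome.

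For VFDs, at the protocol's ICC of 0.03, 34–40 patients per ICU, equal cluster sizes and no gain from matching, the nominal 5% test has a true type I error of about 17–18% (16.6–18.5% by formula). Confidence intervals are too narrow by a factor of about 1.4–1.5. If pairing absorbs an assumed 25–75% of the between-ICU variance, the error is still about 15% down to 8–9%. The direction of the error is the same for the secondary outcomes, but its size cannot be computed from the document.

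**What to change.** Replace the tests named in 2.9.2 with a prespecified analysis that respects the ICU, states how the matched pairs are handled, and uses a small-sample correction suited to 16 clusters.

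- **VFDs.** Several choices are valid: a linear mixed model with small-sample degrees of freedom, an analysis of ICU means, or a within-pair permutation test (2⁸ = 256 allocations). Name one as primary. Estimate the mean difference on which the trial is powered, and drop the normality pre-test as the rule for choosing the test.
- **Binary and time-to-event outcomes.** Use cluster-respecting methods, also with small-sample correction.
- **Software.** Confirm that the named package can run the chosen methods, or name one that can.

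**Cost.** The change is one of wording and possibly software. No new data items are needed, since each patient's data code already carries the ICU number. Intervals will be wider. Power for a one-day difference at 648 patients will be about 61–74%, depending on degrees of freedom and with no gain from matching, rather than the stated 80%. The protocol should say so; the shortfall is no reason to keep an invalid test.

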## Discussion

3

In the current clinical practice of PSV, a combination of VT and RR is recommended as the target inspiratory support level (7, 8), and many centers follow this strategy (36–38). However, previous studies have shown that excessive support of inspiratory pressure may not be uncommon based on this approach (13, 14). Additionally, a mismatch between patient demand and ventilatory support is the main reason for patient-ventilator asynchrony, which may make weaning difficult and lead to prolonged mechanical ventilation (39, 40). Therefore, monitoring the patient’s inspiratory effort and tailoring the pressure support to match the effort is a reasonable solution.

Previous studies have suggested that the PMI, which can conveniently be obtained on the ventilator screen, could reliably detect low and high inspiratory effort (18–20). In patients undergoing PSV, our study group also found the range of PMI to predict the high and low contribution of a patient’s effort and the feasibility of pressure support adjustment according to the PMI target (20).

In this cluster RCT, the major intervention is comparing the pressure support setting and adjustment strategy between the VT/RR target (traditional strategy) and the PMI target (modified strategy). Randomization within one ICU may result in confusion among staff caring for the patients and a high likelihood of crossover during the study. Therefore, we chose a cluster RCT design rather than an individual RCT to avoid contamination.

The design of the study procedures is based on two main principles: rigorousness and feasibility. In the study protocol, we predefine standard clinical management of PSV, including the initiation of PSV, PSV setting strategy depending on the grouping, rescue backup of controlled ventilation modes, and weaning and extubation process. These components of the procedures are in accordance with the international guidelines (25–28) and followed by the participating ICUs. Additionally, we reinforce these procedures through comprehensive training before the initiation of the trial and the use of active and passive measures of quality control during the study. On the other hand, for the feasibility of the study, we mainly focus on the application of pressure support setting and adjustment strategy with a limited burden on the intervention workload.

A clear algorithm for pressure support adjustment is designed in either the VT/RR-targeted or PMI-targeted group (Figure 2). In both groups, safety considerations are schemed in case the adjusted pressure support level does not achieve the target. We anticipate that these algorithms will be highly operable in the study’s performance.

Post-hoc analysis will be performed by predefine stratification into a subgroup with high inspiratory effort, a subgroup with ARDS, and a subgroup with a long duration of controlled ventilation before enrollment. Such subgroup analysis may help identify patient populations that may benefit from pressure support adjustment strategies based on effort assessment.

There are two major potential problems in the present study. The first is the accessibility of a stable plateau Paw during end-inspiratory occlusion and the measurement of PMI. This maneuver is not widely applied in clinical practice because airway occlusion may induce an unstable plateau Paw (32). However, relatively high incidences of unstable occluded Paw were reported in retrospective PMI analyses in which the main purpose was not the measurement of plateau pressure in the original studies (16, 41). In our previous study, we integrated a training and quality control approach emphasizing several key points during the end-inspiratory occlusion (check of air leak, observation of zero flow during the occlusion, and a length of occlusion longer than 2 s) (19, 20). Incidence of immeasurable plateau pressure decreased to less than 10%. These results were confirmed by a recently published study by another research group (18). Second, in our experience and results from published investigations (42), it seems that PSV is only used as a mode for preparing the liberation of mechanical ventilation in many Chinese ICUs. However, an international prospective cohort study demonstrated that the use of PSV had increased over the past two decades and became the most commonly used assisted ventilation mode during the acute phase of critical illness (2). As mentioned above, the training in standard clinical management of mechanical ventilation, especially for the initiation of PSV, will be emphasized before the start of the trial. We hope this approach might enrich our recruitment. However, because there is substantial heterogeneity in the mechanically ventilated patients, subtypes of patients may have a different response to the support pressure adjustment. For example, patients with AHRF are quite different from those with ARDS (43). Although we predefined post-hoc subgroup analysis, future work with prespecified subgroups will be needed and helpful, such as patients with abnormal low or high inspiratory drive and effort.

In conclusion, IT-PSV is a cluster RCT that will evaluate the effect of a PMI-targeted pressure support setting and adjustment strategy on the duration of mechanical ventilation in patients undergoing PSV. If positive, it will provide a new physiological-based PSV management that could potentially facilitate protective assisted ventilation.

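### The subgroup analyses aim to find who benefits, but the only tests named in section 2.9.2 are two-group comparisons, which cannot show that the effect differs between strata

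*Protocol article*

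**What the plan says.** Section 2.9.2 of the protocol article, headed Statistical analysis plan, names these tests: chi-squared or Fisher's exact for categorical variables, Student's t or Mann–Whitney for continuous variables, and log-rank for time-to-event variables. It then states: "The patients will be stratified *a priori* into subgroups with", and lists three splits: high against intermediate and low respiratory drive by P0.1, ARDS against non-ARDS, and long against short prior controlled ventilation, cut at the median of all enrolled patients. The section closes with one rule: "A *p* value of less than 0.05 is considered statistically significant".

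The Discussion gives the purpose: "Such subgroup analysis may help identify patient populations that may benefit from pressure support adjustment strategies based on effort assessment". There it names one side of each split only (high effort, ARDS, long controlled ventilation). It adds that subtypes of patients may respond differently to the adjustment strategy.

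No interaction test, model or contrast between strata is mentioned. Nor is it stated that the listed tests will be run inside each stratum, or that they are the only subgroup analysis.

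**The concern.** The stated aim is comparative: to find the patients for whom the strategy works, as distinct from those for whom it does not. A two-group test run within a stratum has the null hypothesis of no effect in that stratum. Two such tests side by side do not test whether the effects are equal. Each stratum holds only part of a sample sized for the whole trial, so its power is moderate. Even when the effect is the same everywhere, one stratum will often reach p < 0.05 while its complement does not.

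At stake is a false statement about who benefits, for example that the strategy works in ARDS and not outside it. Allowing for clustering within each stratum does not remove the problem. The primary comparison is not affected.

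**Working it through.** **Inputs (section 2.9.1).** Mean and SD: "VFDs in Chinese academic hospitals was 19 ± 3.3 days". Target: "detect a one-day increase in VFDs with a type I error (Alpha) of 0.05 and a power of 80"%. Intra-cluster correlation 0.03, 16 ICUs, about 40 patients per ICU. Two-sided alpha is assumed, and it reproduces the plan's figure.

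**The plan's own figures.**
- Per arm: 2 × (1.960 + 0.842)² × 3.3² / 1² ≈ 171, so 342 in total. The plan says: "An individual RCT will require 342 patients".
- Design effect: 1 + (342/16 − 1) × 0.03 = 1.611, and 342 × 1.611 = 551.
- 551 / 0.85 = 648.

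All three reproduce.

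**Analytic check: uniform one-day effect, 342 effective patients divided between two strata.** With n effective patients per arm in a stratum, power = Φ(1 / (3.3 × √(2/n)) − 1.96). With stratum powers a and b, the chance that exactly one is significant is a(1 − b) + b(1 − a), treating the two tests as independent.

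| Split | n per arm | Power | Exactly one significant |
|---|---|---|---|
| 50/50 | 85.5 / 85.5 | 51% / 51% | 50% |
| 30/70 | 51.3 / 119.7 | 34% / 65% | 55% |
| 20/80 | 34.2 / 136.8 | 24% / 71% | 61% |

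Only the 50/50 row is fixed by the document, through the median rule. The other rows are assumed sizes for the P0.1 and ARDS strata.

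**Simulation.** 16 ICUs, correlation 0.03, the same true one-day effect in both strata, normal outcomes, pair matching ignored, 8,000 trials per row. Cluster sizes are 40 (the stated average) and 34 (551/16 = 34.4).

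| Per ICU | Split | Exactly one significant, patient-level t-test | Exactly one significant, test on ICU means | Interaction test rejects |
|---|---|---|---|---|
| 40 | 50/50 | 31% | 40% | 5.1% |
| 40 | 30/70 | 40% | 43% | 4.9% |
| 34 | 50/50 | 34% | 40% | 5.4% |
| 34 | 30/70 | 44% | 43% | 4.7% |

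The interaction test is a t-test on the within-ICU difference between strata. Every rejection in the last column is false, because the true effects are equal.

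The simulated figures lie below the analytic ones for two reasons. The patient-level test ignores clustering, so it rejects more often in both strata. For the ICU-mean test at 40 per ICU and 50/50, both strata were significant in 32.1% and exactly one in 39.6%, so power per stratum is 32.1 + 39.6/2 = 51.9%. Independent tests would then disagree in 2 × 0.519 × 0.481 = 50%. The two strata share their ICU effects, which brings this down to 40%.

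**Power of the remedy.** On 342 effective patients the overall effect has standard error 3.3 × √(2/171) = 0.357 day. For a 50/50 split the interaction has 2 × 0.357 = 0.714 day. Power for a one-day difference in effects is Φ(1/0.714 − 1.96) = 29%. The difference detectable with 80% power is 2.80 × 0.714 = 2.0 days.

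This may be somewhat pessimistic, because a common ICU effect cancels in a within-ICU contrast. At best, with 640 patients and residual SD 3.3 × √0.97 = 3.25, the standard error is 2 × 3.25 × √(2/320) = 0.514 and power is Φ(1/0.514 − 1.96) = 49%, before allowing for the few degrees of freedom that 16 ICUs leave. Power is low on either reckoning.

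**The case against.** The strongest reply is that this rests partly on silence. A reader might infer that the plan uses within-stratum tests alone, or that no contrast between strata is planned. The article says neither. Section 2.9.2 lists its general tests and its three splits separately, names both sides of each split, and excludes nothing. A separate analysis plan may exist and could hold an interaction test. That stands, and it is why the point is put conditionally.

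The Discussion is also cautious. It says the analysis may help, calls it post-hoc, and asks for further work with prespecified subgroups. A reader might infer that the trial will steer the strategy to ARDS or high-drive patients on a single p-value. No decision rule of that kind appears.

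A reader might also combine the per-split figures into a chance that at least one of the three splits misleads. The document gives no stratum sizes for P0.1 or ARDS and nothing on how the three factors overlap, so such a figure would rest on invented inputs. The excess of significant strata when there is no effect at all is mainly a matter of multiplicity and ignored clustering, which are separate issues.

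What the reply does not remove is the mismatch in the text. A section headed Statistical analysis plan names only tests of an effect within a comparison, while the Discussion sets a question about differences between strata. Caution in wording does not change what a within-stratum p-value measures.

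**Conclusion.** The point holds in conditional form. The named tests cannot answer the stated subgroup question. If they are applied within strata, a uniform one-day effect will look confined to one side of a given split in roughly 31–44% of trials at a correlation of 0.03 (about 50% analytically for the median split), against about 5% false signals from an interaction test. These figures assume two-sided alpha, normal VFDs with SD 3.3, a common intra-cluster correlation, no gain from pair matching, and P0.1 and ARDS strata between 30/70 and 50/50.

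The document does not support saying that an interaction analysis has been ruled out. The consequence is limited to secondary, hedged analyses, but the change is cheap and the risk of a misleading subgroup statement is substantial.

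**What to change.** In section 2.9.2, state that each of the three subgroup questions is answered by a cluster-adjusted strategy-by-subgroup interaction on VFDs. This can be a comparison between arms of the within-ICU difference between strata, or an interaction term in a model with ICU effects. Report both stratum effects and their difference with 95% confidence intervals, and label the analysis exploratory.

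Reword the subgroup paragraph of the Discussion so that both sides of each split are named and no population is identified as benefiting from a within-stratum p-value alone. If a separate analysis plan already provides the interaction, one sentence in 2.9.2 and the rewording are enough.

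The cost is wording and three extra model terms, with no new data. The drawback is the low power shown above: 29% for a one-day difference in effects on the plan's effective sample, with about 2 days detectable at 80%. Fewer subgroup statements will be possible, and a non-significant interaction must not be read as proof that the effect is uniform.
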